This study is designed to fill gaps identified in existing research in this field, specifically by exploring how, when and in what context feedback works best to influence medication error reporting behaviour among nurses. The findings of this study will add to knowledge about characteristics, including the content and intensity (dose) of audit and feedback that are important in influencing health professionals’ behaviour regarding reporting of medication errors. Measurement of health professionals’ perceptions of organisational context will enable us to assess the extent to which contexts perceived as more favourable are associated with increased reporting of errors.

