### Pilot testing an intervention to improve medication error reporting

Consistent with the UK Medical Research Council guidelines for the development of complex interventions [44], we conducted a small study in a 32-bed acute care ward at a large private hospital to inform development and undertake pilot and feasibility testing of medication chart audit tools and the SMART feedback intervention.

Baseline audit data were collected on key aspects of medication administration. At baseline, all ward nursing staff were invited to complete the Alberta Context Tool [45, 46], a questionnaire designed to elicit perceptions of the work context (including culture, leadership and feedback mechanism). The feedback intervention comprised Microsoft PowerPoint^©^ presentations to display audit data and survey results in graph form, coupled with face-to-face discussions about the results. Additionally, copies of the results slides were displayed on the ward for staff to view. The feedback was augmented with information about the definition of a medication error, the importance of reporting medication errors and near misses and the importance of a no-blame culture.

Medication administration audit data were collected 2 months following the feedback intervention, and staff were re-surveyed about their perceptions of the work context 6 months following collection of the baseline data. The frequency of medication errors in the 12 months prior to the intervention and in the 6 months post-intervention was compared. We found an 80 % increase in the reporting of medication errors and a statistically significant improvement in perceptions of evaluation and feedback mechanisms (including access to data, review, monitoring and benchmarking). The considerable increase in frequency of error reporting in the post-intervention phase highlighted the potential for this intervention to improve error reporting across the organisation and beyond and the importance of more rigorous testing of the intervention.

This pilot work underpins the study that is the subject of this protocol. The premise upon which this study is built is that comprehensive reporting of medication errors is necessary to inform interventions and process redesign to prevent further errors occurring.

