## Methods

This controlled interrupted time series study design incorporates two pairs of matched wards at an acute care hospital with randomisation of two wards to the control group and two wards to the intervention group. Nurses in the intervention group will receive the SMART intervention (feedback of medication error audit data).

We will adopt the National Coordinating Council for Medication Error Reporting and Prevention standard definition of a medication error: “any preventable event that may cause or lead to inappropriate medication use or patient harm while the medication is in the control of the health care professional, patient, or consumer” [47].

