### Setting and sample

This study will take place at a large, not-for-profit Australian private health provider. Four acute care wards will be included in the study. The wards will be matched as closely as possible according to clinical casemix (diagnostic group and average length of stay).

A key stakeholder reference group will be established to determine the preferred feedback methods and mechanism (the design of the feedback report and how it is presented to staff). This group was instrumental to feedback design in the pilot study and will include clinical nurses and representatives from nursing management, pharmacy and medicine (*n* = 10).

Managers (*n* = 4) and nurses (*n* = 160) working in the four participating wards will be invited to participate in this study.

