#### Survey data sources

Two other sources of data are surveys of nurse participants:The Alberta Context Tool (ACT) will be administered twice to nurses in all four wards: at baseline, prior to introduction of the feedback reports and 12 months following baseline data collection [45, 46].The post-feedback survey will be administered four times to intervention ward participants (1 week following each feedback report) [11].

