### Analysis

Quantitative methods will be used to analyse the survey data. Analysis will involve the use of simple descriptive statistics, including frequencies and cross tabulations, and bivariate analysis using correlations. Interrupted time series analysis will be used to assess for change over time in response to the feedback. Outcomes will include error rates identified during the point-prevalence chart audits and the error report rates identified from RiskMan data. These data will be aggregated at ward level.

We will also examine RiskMan data for the 12-month period prior to the intervention. Intervention dose will be the main predictor, operationalised as the number of nurses on the ward who self-report reading the feedback reports. Aggregated at ward level, scores for the eight dimensions of organisational context will also be included as predictors of medication error reporting rates. Multivariate regression analyses will include cluster correction to adjust for ward and site effect. Content analysis will be used to analyse string variable responses to open-ended questions about suggestions to improve reports. Qualitative data will be analysed using content and thematic analysis techniques.

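### Eight ward-level context scores cannot be separated with four wards: if entered jointly, as the Analysis section most naturally reads, their coefficients are not identified and aim 3 has no estimable regression

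*Protocol article*

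**What the plan says.** The Setting and sample section fixes the number of units: "Four acute care wards will be included in the study". The Methods opening gives the allocation: "two pairs of matched wards at an acute care hospital with randomisation of two wards to the control group and two wards to the intervention". Under Survey data sources, "The Alberta Context Tool (ACT) will be administered twice to nurses in all four wards", at baseline and at 12 months.

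The Analysis section sets the outcomes (chart-audit error rates and RiskMan report rates) and says of them: "These data will be aggregated at ward level". It then names the predictors: "Intervention dose will be the main predictor, operationalised as the number of nurses on the ward who self-report reading the feedback reports", followed by "Aggregated at ward level, scores for the eight dimensions of organisational context will also be included as predictors of medication error reporting rates". The regression is described as multivariate, with a cluster correction for ward and site.

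This regression is the quantitative route to aim 3, which seeks features of the organisational context that go with error reporting after feedback. The Background says that measuring context will let the investigators "assess the extent to which contexts perceived as more favourable are associated with increased reporting of errors".

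**The concern.** Aggregation leaves one value per dimension per ward at each ACT wave. The number of distinct context values is then set by wards and waves, not by how often the outcome is recorded. The plan asks for eight separate context effects from four wards.

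When predictors outnumber the distinct score sets, infinitely many sets of coefficients fit equally well. Software then drops terms or picks one solution by an internal rule. A published statement that culture, leadership or any other dimension goes with reporting would reflect that rule and not the data. What is at stake is the quantitative answer to one of the three stated aims.

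**Working it through.** The article gives no sample size, power or alpha for this analysis, so there is no stated figure to reproduce. The check is whether the coefficients are identified.

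**Inputs from the article**
- Wards: 4, of which 2 are intervention wards (Methods; Setting and sample).
- ACT waves: 2 (Survey data sources).
- Context dimensions: 8 (Instruments; Analysis).
- Dose: up to 4 readings per intervention ward, from the post-feedback survey.
- Outcome rows: weekly RiskMan data for 12 months, 4 × 52 = 208. With the 12 months before the intervention, 4 × 104 = 416.

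**Coefficients.** Intercept + 8 dimensions = 9. With dose, 10.

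**Upper limit on rank.** The rank of the block made of the intercept and eight scores cannot exceed the number of distinct score vectors:
- one wave, or the mean of two: 4 × 1 = 4, below 9;
- both waves: 4 × 2 = 8, still below 9.

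Interpolating linearly between waves makes every week's row different. Each row is still a weighted mix of that ward's two vectors, so the limit stays at 8.

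**Numerical check.** Rank was computed with simulated, distinct ward scores and a dose that changes by quarter.

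| Layout | Intercept + 8 scores (9 needed) | Plus dose (10 needed) |
|---|---|---|
| 4 ward rows | 4 | 4 |
| 8 ward-by-wave rows | 8 | 8 |
| 208 or 416 weekly rows, one score per ward | 4 | 5 |
| 208 or 416 weekly rows, both waves (step or linear) | 8 | 9 |

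Adding time terms leaves every weekly layout deficient; the best cases are 10 of 11 and 12 of 13. Restricting to the two intervention wards over four quarters, with baseline scores, gives 3 of 10.

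**Dose.** In the weekly layouts, adding dose raises the rank by one (4 to 5, 8 to 9). Its column is therefore not a combination of the context columns, and its coefficient can be estimated there. In the two aggregated layouts it adds nothing.

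**One dimension at a time.** The critical correlation is |r| = t / √(df + t²), with df = n − 2 and two-sided alpha 0.05 (assumed).
- n = 4 wards: df = 2, t = 4.303, |r| = 4.303 / √(2 + 18.51) = 0.950.
- n = 8 ward-by-wave points treated as independent, which is optimistic: df = 6, t = 2.447, |r| = 2.447 / √(6 + 5.99) = 0.707.

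**The case against.** The best defence is that the article never says all eight scores enter one equation. It speaks of regression analyses in the plural, it is a condensed account, and the order and manner of entry are often left to an analysis plan. That stands as a condition on the finding. Joint entry is still the natural reading: the scores are added to dose in one description of a multivariate regression, and the simple correlations in that section are tied to the survey data. The alternative, one dimension at a time, runs but needs near-perfect correlation.

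Two further replies fail. Weekly data add outcome rows but no new context values. Cluster correction changes standard errors, not identifiability; it would rest on four clusters, and a site effect has no meaning at a single site.

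A reader might infer more than the article supports:
- *That the whole regression fails, dose included.* Dose can vary by quarter within a ward, so its coefficient may be estimable.
- *That the fit will be perfect.* That holds only for aggregated rows (4 − 4 = 0 or 8 − 8 = 0 residual degrees of freedom). With 208 weekly rows and rank 5 or 9, 203 or 199 remain.
- *That adjusting for context removes part of the intervention effect*, because the pilot saw "a statistically significant improvement in perceptions of evaluation and feedback mechanisms". The article does not say that the 12-month ACT will be a predictor, and the pilot was a before-and-after comparison on one ward.
- *That ward fixed effects make matters worse.* None are planned.

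**Conclusion.** The point holds for the separate context coefficients under joint entry. At least one of the nine coefficients has no support in the data if both ACT waves are used (rank 8 of 9), and five have none if one wave is used (rank 4 of 9). This follows from the numbers of wards, waves and dimensions and needs no assumption about effect sizes or variances. The 0.95 threshold for one-at-a-time entry assumes two-sided alpha 0.05.

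The controlled interrupted time series that tests the intervention is untouched. The Limitations section mentions a single site and a small sample but not this problem, so the stated quantitative route to aim 3 fails as written.

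**What to change.** In the Analysis section:
- remove the eight ward-level context scores from the regression;
- report each ward's ACT profile descriptively beside its reporting rates;
- state that the quantitative part of aim 3 is descriptive and that four wards cannot separate eight dimensions.

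Bring the Background sentence on favourable contexts and increased reporting into line by withdrawing the claim of association. If any context predictor is kept, name one baseline ACT score in advance and label the result exploratory.

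The cost is a change of wording. It needs no new data, which matters because collection began in February 2015. The loss is that no inferential claim can be made about which context features go with reporting, so aim 3 then rests on descriptive and qualitative data. Moving to nurse-level intention would not recover that claim: it replaces the outcome named in aim 3 with a different one, and the article's Theory of Planned Behaviour section itself notes that intention is not always followed by behaviour.

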**Methods/design:**

A quasi-experimental design, incorporating two pairs of matched wards at an acute care hospital, is used. Randomisation occurs at the ward level; one ward from each pair is randomised to receive the intervention. A key stakeholder reference group informs the design and delivery of the feedback intervention. Nurses on the intervention wards receive the feedback intervention (feedback of analysed audit data) on a quarterly basis for 12 months. Data for the feedback intervention come from medication documentation point-prevalence audits and weekly reports on routinely collected medication error data. Weekly reports on these data are obtained for the control wards. A controlled interrupted time series analysis is used to evaluate the effect of the feedback intervention. Self-report data are also collected from nurses on all four wards at baseline and at completion of the intervention to elicit their perceptions of the work context. Additionally, following each feedback cycle, nurses on the intervention wards are invited to complete a survey to evaluate the feedback and to establish their intentions to change their reporting behaviour. To assess sustainability of the intervention, at 6 months following completion of the intervention a point-prevalence chart audit is undertaken and a report of routinely collected medication errors for the previous 6 months is obtained. This intervention will have wider application for delivery of feedback to promote behaviour change for other areas of preventable error and adverse events.

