### Strengths and limitations of study

This study will add to the evidence base on use of audit with feedback among nurses. In particular, it will promote understanding of the potential for feedback to promote behaviour change regarding medication error reporting, how and in what forms nurses prefer to receive feedback and how the contexts in which nurses work affect their ability to report medication errors. Additionally, the study will contribute knowledge about the accuracy of medication error reporting, comparing hospital incident reporting system data with evidence of administration errors in medical record documentation.

Limitations of this study need to be acknowledged. The study is to be conducted at a single site, with a relatively small sample. While we will match intervention and control wards as closely as possible on the basis of clinical casemix, there is no guarantee that matched wards within the same hospital will be entirely similar (e.g*.*, differences in ward culture, patient acuity/type, staffing turnover); hence, we will adjust for differences using the available data. Feedback will be constructed based upon advice from the key stakeholder group. It is possible that this format will not suit all nurses, and so, some staff may not find the feedback meets their needs and may discount it as a result. Behaviour change in reporting may also occur as a result of other variables (such as policy changes and/or serious medication incidents that make staff more aware/anxious about reporting). Hence, not all behaviour change may be attributable to the feedback intervention. Potential for contamination of the control group exists; however, the organisation has a stable nursing workforce with a vacancy rate of less than 5 %. Thus, permanent staff do not commonly work across different wards, thereby limiting the risk of contamination.

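### The regression adjustment names a site effect that one hospital cannot supply and leaves out the matched pair within which wards are randomised

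*Protocol article*

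**What the plan says.** The Analysis section states that the multivariate regressions will use "cluster correction to adjust for ward and site effect". That sentence follows the description of intervention dose and the eight context dimensions as predictors. The interrupted time series analysis is named in the paragraph before it, without model terms.

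The design is described elsewhere in the article:

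- Methods: "two pairs of matched wards at an acute care hospital with randomisation of two wards to the control group and two wards to the intervention" arm.
- Abstract, Methods/design: "Randomisation occurs at the ward level; one ward from each pair is randomised to receive the intervention".
- Setting and sample: "Four acute care wards will be included in the study", and "The wards will be matched as closely as possible according to clinical casemix", meaning diagnostic group and average length of stay.
- Strengths and limitations of study: "The study is to be conducted at a single site, with a relatively small sample".

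The matched pair does not appear in the Analysis section. The limitations section promises in general terms to adjust for differences between wards with whatever data are at hand. It names neither the pair nor the matching variables.

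**The concern.** The article lists the levels its regressions will adjust for, and the list does not fit the design. Site has one level. Pair, which has two levels and defines the restriction on the randomisation, is absent.

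What is at stake is how the comparison deals with change over time. Matching puts one ward of each casemix in each arm. If error reporting shifts in one type of casemix for reasons unrelated to feedback, the matched control ward shows the same shift, and a within-pair comparison removes it. A pooled comparison of arms removes it fully only if that casemix carries the same weight in both arms. Ward effects do not help here: they take out differences in level, whereas the time series measures change.

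**Working it through.** The article gives no figure for this point, so there is nothing to reproduce. The inputs from the documents are 4 wards, 2 pairs, 1 hospital, and one ward per pair randomised. Report volumes and trends are not given; those below are assumptions.

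**1. Site.** With one site, its indicator is 1 for every ward and coincides with the intercept. The ward-level design matrix [intercept, treatment] has rank 2, and [intercept, treatment, site] also has rank 2. No site effect or between-site variance can be estimated.

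**2. Pair.** [intercept, treatment, pair] has rank 3, so pair is estimable. With 4 ward-level summaries, 4 − 3 = 1 residual degree of freedom remains (two-sided 5% critical t of 12.71, against 4.30 with 2 degrees of freedom when pair is left out).

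**3. Does ward cover pair?** If ward means fixed effects, [ward] and [ward, pair] both have rank 4, so the main effect of pair is absorbed. Pair-by-period change is not. If ward means only a clustered variance correction, even the main effect is not absorbed.

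**4. Size of a possible bias.** Assume reports in pair A rise by 40% in both arms for reasons unrelated to feedback, pair B is unchanged, and feedback has no effect. Let s be pair A's share of baseline report volume within an arm. A Poisson model with ward effects and group-specific post terms gives

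spurious rate ratio = (1 + 0.4 × s in the intervention arm) / (1 + 0.4 × s in the control arm).

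| Weekly means, intervention (A, B) | Weekly means, control (A, B) | Shares s | Ratio |
|---|---|---|---|
| 2, 2 | 2, 2 | 0.50, 0.50 | 1.20/1.20 = 1.00 |
| 4, 2 | 2, 1 | 0.67, 0.67 | 1.267/1.267 = 1.00 |
| 3, 2 | 2, 3 | 0.60, 0.40 | 1.24/1.16 = 1.07 |
| 3, 1 | 2, 2 | 0.75, 0.50 | 1.30/1.20 = 1.08 |
| 2, 1 | 1, 2 | 0.67, 0.33 | 1.267/1.133 = 1.12 |
| 3, 1 | 1, 3 | 0.75, 0.25 | 1.30/1.10 = 1.18 |

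Exchanging the arms in the last row gives 1.10/1.30 = 0.85, so the bias can go either way. With pair-by-period terms the contrast is 1.4/1.4 = 1.00 in pair A and 1.0/1.0 = 1.00 in pair B in every row.

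**5. What the design can support.** Randomising within pairs allows 2 × 2 = 4 allocations. The smallest randomisation p is 1/4 = 0.25 one-sided and 2/4 = 0.50 two-sided.

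**The case against.** Four arguments can be made on the other side.

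- **A one-level site term is harmless.** This stands. Deleting it alone changes no estimate. It matters as a sign that the adjustment levels were not matched to the design.
- **The quoted sentence concerns the multivariate regressions, not the time series model.** This stands in part. The article does not state the terms, link or weights of the time series model, so the Poisson contrast above is an assumed form. Averaging the wards' log rate ratios with equal weights gives 1.00 even at the most unbalanced volumes shown.
- **Pair-by-time terms are detail that an article may leave to the full protocol or the SAP.** This would hold if the article were silent on adjustment. It is not silent: it lists the levels, includes one that does not exist and omits the one used to randomise.
- **The matching already protects.** This stands in part. Each arm holds one ward of each casemix, and at equal shares the bias is nil without any pair term.

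A reader might go further and infer that the matching gives no protection, or that unequal volumes within a pair are enough to cause bias. The row with 4, 2 against 2, 1 shows otherwise: volumes differ within both pairs, the shares agree, and the ratio is 1.00. A reader might also infer that ignoring pairs inflates false positives. In a simulation of an unpaired, equally weighted ward-level analysis at nominal 5%, type I error was 5.0%, 2.9% and 1.8% for an assumed pair SD of 0, 1 and 2 times the ward SD. That is conservative and inefficient, not inflated.

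**Conclusion.** The point holds. The article names an adjustment for site that a single-hospital study cannot make, and its analysis omits the matched pair. The first is an internal contradiction with no numerical consequence by itself. The second leaves a pooled contrast open to bias under three conditions together: a trend specific to one casemix, shares of report volume that differ between arms, and pooling that weights by volume.

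For an assumed 40% trend in one pair, the spurious ratio runs from 1.00 through 1.07 to 1.18 over the volumes considered. The figure of 1.18 needs a threefold imbalance in opposite directions in wards chosen to be alike, so it should not be read as the expected bias. Wards are matched on casemix, however, not on reporting volume, so equal shares cannot be taken for granted either. The documents do not support calling this the main threat to the study. The limitations section itself points to policy changes, serious incidents and contamination, and the small number of wards limits inference whichever model is used.

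**What to change.** In the Analysis section, replace site with pair. State that the intervention effect is estimated within pairs, by pair-by-period terms or within-pair contrasts in the weekly model, and that the two pair-specific effects will be reported side by side.

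No new data are needed. Twelve months before and twelve months during the intervention give about 4 × 104 = 416 ward-weeks, assuming the baseline extract can be split by week, so a few extra parameters are affordable in the weekly model. That count should not be mistaken for precision about the intervention effect: at ward level only 1 residual degree of freedom remains. The change does not overcome the limits of inference from four wards, and the article should acknowledge this, including the minimum two-sided randomisation p of 0.50.
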